### 9.2.3 Serious Adverse Events

All SAEs that occur during the trial will be captured on the CRF.

**Serious Adverse Event:** An SAE is defined as an AE that meets one of the following conditions:

- Death.
- Life threatening (subject at immediate risk of death.) *(The term “life-threatening” in the definition of “serious” refers to an event in which the patient was at risk of death at the time of the event; it does not refer to an event that hypothetically might have caused death if it were more severe).*
- Requires inpatient hospitalization or prolongation of existing hospitalization. *(Continuation of stay in the isolation unit beyond 7 days post-administration of either dose of study vaccine or placebo because of late detected viral shedding in a subject shall not be considered a “prolongation of existing hospitalization” for SAE recording or reporting.)*
- Results in congenital anomaly/birth defect. *(Only in the case of a woman becoming pregnant during the study period after administration of at least one dose of study vaccine. All pregnancies must be followed to term and outcome reported to the Sponsor, PVS and regulatory agencies.)*
- Results in a persistent or significant disability or incapacity.
- Important medical events that might not result in death, be life threatening, or require hospitalization might be considered SAEs when, based upon appropriate medical judgment, the event might jeopardize the well-being of the subject and require medical or surgical intervention to prevent one of the outcomes listed above. *(Medical and scientific judgment should be exercised in deciding whether reporting these events is appropriate.)*

All SAEs occurring within one month of any study vaccination must be reviewed and evaluated by a study clinician (SAE relationship to study vaccine must be evaluated as outlined in Section 9.2.3) and recorded on an SAE form and reported (as specified in Section 9.3). All such SAEs should also be followed until satisfactory resolution or until the investigator deems the event to be chronic or the patient to be stable.

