### **3.2 Study Outcome Measures**

#### **3.2.1 Primary Outcome Measures**

The safety profile will be parameterized as the proportion of subjects experiencing adverse events (AEs) of the following four categories:

- 
- Immediate reactions occurring within two hours of administration of any dose, measured as observed by study staff or reported by the subject to study staff.
  - Adverse events commonly associated with intranasal vaccination (solicited local and systemic reactions) occurring greater than two hours after administration of any dose of study vaccine or placebo through 7 days following any dose, measured as observed by study staff or reported by the subject to study staff.
  - All other adverse events (including unsolicited events) occurring during the 7 days following any dose, measured as observed by study staff or reported by the subject to study staff. This includes abnormal laboratory findings from blood and urine specimens collected on Days 7 and 35.
  - All serious adverse events (SAEs) occurring within 4 weeks of receipt of any dose, as observed by study staff, reported by the subject to study staff, or noted by the subject on a diary card. This includes abnormal laboratory findings from blood and urine specimens collected on Days 28 (pre-vaccination) and 56.

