### 5.1 Subject Inclusion Criteria

Questions about eligibility must be addressed prior to enrollment. The following criteria must be met before a subject may be enrolled for participation:

- Legal male or female adult 18 through 49 years of age at the enrollment visit.
- Literate and willing to provide written informed consent.
- Free of obvious health problems, as established by the medical history and screening evaluations, including physical examination.
- Capable and willing to complete diary cards and willing to return for all follow-up visits
- Willing to comply with the rules of the isolation unit (including willing and able to take oseltamivir influenza antiviral medication, should that be recommended by a study physician).
- For females, willing to take reliable birth control measures throughout the entire period of participation in the study.

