## 9.3 Reporting Procedures

### 9.3.1 Serious Adverse Events

All SAEs occurring within one month of any study vaccination must be documented and reported to PVS or its designate, even if the investigator considers that the SAE is not related to treatment. The study clinician will complete a **Serious Adverse Event Form** within the following timelines of such events:

- All deaths and immediately life-threatening events, whether related or unrelated, will be recorded on the Serious Adverse Event Form and sent by fax or email within 24 hours of site awareness.
- SAEs other than death and immediately life-threatening events, regardless of relationship, will be reported via fax by the site within 48 hours of becoming aware of the event.

PVS will be primarily responsible for medical monitoring of serious adverse events documented by the investigator. Details for how review of serious adverse events and other unanticipated problems will be conducted will be contained in an SOP prior to study initiation.

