### 9.3.3 Reporting of Pregnancy

All pregnancies detected among women enrolled in the trial who receive at least one dose of study vaccine or placebo must be reported. All pregnancies must be followed to term and outcome reported to the Sponsor, PVS and regulatory agencies. Unblinding of allocation of treatment of female subjects who become pregnant will not occur until after study completion. No female subjects who become pregnant after receipt of study dose one will be allowed to receive study dose two, regardless of allocation of treatment. Such a subject should be withdrawn immediately from the trial.

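### The birth-defect SAE criterion excludes pregnancies already present at dose one, and the one-month SAE window in 9.2.3 and 9.3.1 leaves it without effect for any term birth

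*Protocol*

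**What the plan says.** Section 9.2.3 lists congenital anomaly or birth defect among the SAE criteria and limits it in a parenthesis: "Only in the case of a woman becoming pregnant during the study period after administration of at least one dose of study vaccine". The same parenthesis says that pregnancies are followed to term and their outcome reported.

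The duties that follow from SAE status are tied to a time window. Section 9.2.3 states "All SAEs occurring within one month of any study vaccination must be reviewed and evaluated by a study clinician", and this covers relationship assessment and the SAE form. Section 9.3.1 states "All SAEs occurring within one month of any study vaccination must be documented and reported to PVS or its designate". Deaths and immediately life-threatening events go in within 24 hours of site awareness; other SAEs are to be "reported via fax by the site within 48 hours of becoming aware of the event". Capture on the CRF is for the trial period: "All SAEs that occur during the trial will be captured on the CRF".

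Section 9.3.3 is wider: "All pregnancies detected among women enrolled in the trial who receive at least one dose of study vaccine or placebo must be reported". It sets no limit on the date of conception. It requires follow-up to term and an outcome report to the Sponsor, PVS and regulatory agencies. It does not mention relationship assessment, an SAE form or a deadline.

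Section 5.2 requires a negative pregnancy test before dosing. Section 8.2.1.2 places the urine tests on Days 0, 28 and 56. Section 5.1 requires women to be "willing to take reliable birth control measures throughout the entire period of participation in the study".

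**The concern.** A birth defect is normally recognised at or near birth, many months after the last dose in an eight-week schedule. A seriousness criterion for birth defects therefore works only if the duties attached to it run that long, and here they stop one month after vaccination.

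The conception clause adds a second gap. An embryo conceived shortly before Day 0 and missed by the Day 0 urine test is present when the live virus is given. Its mother did not become pregnant after a dose, so a later anomaly does not meet the definition.

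Safety is the primary objective of this phase I trial. At stake is whether an anomaly in an exposed pregnancy gets a required causality judgement and a reporting clock. The SMC is affected too, since section 9.6.2 makes SAEs its primary focus.

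**Working it through.** The plan states no figure to reproduce. The check is date arithmetic plus a comparison of three sections.

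**Inputs from the protocol**
- Doses on Day 0 and Day 28 (section 6.2.1).
- SAE duties run for one month after any vaccination (sections 9.2.3 and 9.3.1), taken here as up to 31 days.
- Final visit on Day 56 (section 7.2.19). The second sub-cohort starts two weeks after the first (section 4), and the trial ends with the last subject's last visit (section 5.5.1).
- Forty subjects, randomised 3:1 (section 4), with equal numbers of men and women as a recruitment aim (section 14.4).

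**Assumptions not in the documents**
- Term birth comes 35 to 40 weeks after conception: 35 × 7 = 245 to 40 × 7 = 280 days.
- An undetected pregnancy at dose one was conceived between Day −14 and Day 0.

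**End of the SAE window**
- After two doses: 28 + 31 = Day 59.
- After dose one only: 0 + 31 = Day 31. Section 9.3.3 bars a woman found pregnant after dose one from dose two.

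**Date of a term birth**
- Conception from Day −14 to Day 0 (outside the criterion): −14 + 245 = Day 231 to 0 + 280 = Day 280.
- Conception from Day 1 to Day 56 (inside the criterion): 1 + 245 = Day 246 to 56 + 280 = Day 336.

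**Smallest gap between window end and birth**
- Conceived before dose one, two doses given: 231 − 59 = 172 days.
- Conceived before dose one, dose two withheld: 231 − 31 = 200 days.
- Conceived after dose one, two doses given: 246 − 59 = 187 days.

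The result does not depend on the exact length of pregnancy. For a birth to fall inside the window, even from the earliest assumed conception, it would have to occur within 59 + 14 = 73 days of conception. CRF capture during the trial does not help either: for a first sub-cohort subject the trial ends at about 56 + 14 = Day 70. The calculation concerns defects found at birth. An anomaly recognised early in pregnancy could in principle fall inside the window.

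**The three sections compared**

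| | 9.2.3 criterion | 9.2.3 and 9.3.1 duties | 9.3.3 |
|---|---|---|---|
| Product named | study vaccine | any study vaccination | vaccine or placebo |
| Conception date | after a dose | not addressed | no limit |
| Time limit | study period | one month | to term |
| Relationship assessment, SAE form, 24/48-hour report | not applicable | required | not stated |

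**Number of women**
- 40 × 1/2 = 20 women if the recruitment aim is met; 20 × 3/4 = 15 on vaccine.

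**The case against.** The strongest reply is that nothing is lost. Section 9.3.3 covers every pregnancy detected after vaccine or placebo, whenever conceived, and its outcome goes to the Sponsor, PVS and regulatory agencies. That stands, and it limits the point to SAE status and the procedures that come with it. A reader might infer that a defect would go unreported; the text does not support that.

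Deadlines and review are also partly left to SOPs. Section 9.3.1 leaves review of SAEs and other unanticipated problems to one, and section 9.3.2 leaves reporting to the ethics committees to another, without a one-month limit. So only the 24- and 48-hour reports to PVS can be called missing. On causality, section 9.2.2 asks for a relationship judgement on all AEs, but the same section speaks of events during the study, so it does not clearly reach a birth months later.

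Three stronger readings are tempting and do not hold.
- That blinded staff could not apply a criterion naming study vaccine. The protocol uses the term loosely for the blinded product: section 9.2.2 has clinicians judge relationship to study vaccine for all AEs, and section 11.2 describes randomised subjects as receiving study vaccines. The difference from 9.3.3 is one of wording.
- That every pregnancy exposed around conception is excluded. Conception after a dose is inside the criterion; only conception before dose one is outside.
- That this is the first trial of a live avian-reassortant vaccine. Section 2.1 describes earlier ones.

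The event is also rare. A negative test is needed before dosing and contraception is required. Participation of about 10 weeks (70 days, against 56 from Day 0 to the last visit) suggests that the contraception rule includes screening. The documents give neither the test's sensitivity nor a conception rate, so no share of undetected pregnancies can be stated.

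**Conclusion.** The point holds in a limited form. As written, the one-month limit means that a defect found at term birth triggers none of the SAE duties in 9.2.3 and 9.3.1. The gap is at least 172 days, given birth 35 to 40 weeks after conception and conception no earlier than Day −14. Separately, the conception clause leaves a pregnancy already present but undetected at dose one outside the SAE definition; that gap arises only if an early pregnancy passes the Day 0 test.

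The consequence is procedural: no SAE status, no required causality assessment, no SAE form and no deadline to PVS for an outcome that will still be reported. Few or no such events are to be expected among about 20 women. No planned primary estimate changes, because the primary outcome counts "All serious adverse events (SAEs) occurring within 4 weeks of receipt of any dose". The case for acting rests on the weight of the event and the small cost of the correction.

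**What to change.** Reconcile 9.2.3 and 9.3.1 with 9.3.3 by two changes of wording.

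1. In 9.2.3, replace the limiting parenthesis with: *in any pregnancy detected after receipt of at least one dose of study vaccine or placebo, whatever the date of conception*. Keep the sentence on follow-up to term.
2. In 9.2.3 and 9.3.1, add: *The one-month limit does not apply to congenital anomalies. These are assessed for relationship, recorded on an SAE form and reported within the stated time of site awareness.*

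The cost is two sentences in a protocol amendment, carried through to the SAE reporting SOP. No visit, test or subject is added, because follow-up to term is already required. The primary outcome window can stay as it is.

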#### **9.2.4 Procedures to be Followed in the Event that of Abnormal Laboratory Test Values**

To the extent possible, all normal ranges for clinical laboratory test results will be pre-specified. All abnormal laboratory test values must be documented as an AE, unless that value was Grade 1 at study entry (Day 0) and has not increased in severity grade. Abnormal test values may be considered an SAE if the value rises to the level of severe (Grade 4). Any value not normalizing by the end of the study (Day 56) should be followed by the investigator, as would be done under normal clinical care circumstances. After termination of the trial, the investigator should assure that the subject is referred for medical follow-up, as appropriate.

## 9.3 Reporting Procedures

### 9.3.1 Serious Adverse Events

All SAEs occurring within one month of any study vaccination must be documented and reported to PVS or its designate, even if the investigator considers that the SAE is not related to treatment. The study clinician will complete a **Serious Adverse Event Form** within the following timelines of such events:

- All deaths and immediately life-threatening events, whether related or unrelated, will be recorded on the Serious Adverse Event Form and sent by fax or email within 24 hours of site awareness.
- SAEs other than death and immediately life-threatening events, regardless of relationship, will be reported via fax by the site within 48 hours of becoming aware of the event.

PVS will be primarily responsible for medical monitoring of serious adverse events documented by the investigator. Details for how review of serious adverse events and other unanticipated problems will be conducted will be contained in an SOP prior to study initiation.

### 9.3.2 Regulatory Reporting

Collected SAEs and AEs will be reported to responsible ethical review committees according to their requested timelines. An SOP for reporting to the responsible committees will be developed with reporting requirements and timelines prior to study initiation. It will be the investigator's responsibility to assure that all reportable events are reported to the proper authority or to PVS and/or the Sponsor in a timely manner and according to the SOP. PVS and/or the Sponsor may assist the investigator with regulatory reporting, per the finalized SOP.

### 9.3.3 Reporting of Pregnancy

All pregnancies detected among women enrolled in the trial who receive at least one dose of study vaccine or placebo must be reported. All pregnancies must be followed to term and outcome reported to the Sponsor, PVS and regulatory agencies. Unblinding of allocation of treatment of female subjects who become pregnant will not occur until after study completion. No female subjects who become pregnant after receipt of study dose one will be allowed to receive study dose two, regardless of allocation of treatment. Such a subject should be withdrawn immediately from the trial.

## 9.4 Type and Duration of Follow-up of Subjects after Adverse Events

SAEs occurring within one month of any study vaccination will be recorded as indicated in the CRF. AEs likely to be related to the product whether serious or not, which persist at the end of the trial will be followed up by the investigator until their complete disappearance. The

investigator will document the date of final disappearance of the AE on a data clarification form.

## 9.5 Halting Rules

Given the long experience with LAIVs, no safety issues are anticipated which would result in the suspension of the study. However, as this study is a phase 1 trial, the trial might be suspended at any time by the Sponsor, PVS, the Russian Ministry of Health, the SMC, any ethical review committee overseeing this study, or by the investigator for any safety concern. This includes, for example, and without limitation, an SAE resulting in death, an unexpectedly high number of persons shedding virus after receipt of any dose, an unusually high rate of SAEs, or an unexpectedly early onset of substantial seasonal influenza virus circulation in the surrounding community. PVS may suspend the study in the event that study conduct is found to be below GCP standards.

Should an SAE occur which is likely related to administration of study vaccine, the decision whether the study should continue per protocol, proceed with caution, be suspended pending further investigation, be discontinued, or be modified and then proceed will be made by the Sponsor and PVS in consultation with the investigators, the SMC, and/or the RF MoH. However, no rules will be prespecified to define these conditions.

If the study is halted, subjects will be contacted immediately explaining why the study has been halted and the implications for their medical well-being.

In the event of the appearance of new data that indicate an increased level of risk to participating subjects, the clinical trial will be suspended until the Sponsor, PVS, the Russian Ministry of Health, the SMC, and all ethical review committees have reviewed relevant data and agreed that the trial may proceed.

## 9.6 Safety Oversight by a Safety Monitoring Committee

Additional safety oversight will be conducted by a Safety Monitoring Committee (SMC). The SMC will operate under rules of a SMC-approved charter that will be written or finalized at the organizing meeting of the SMC (first meeting). PVS will draft this charter, and the SMC will approve it, after any modification by the SMC. The draft charter will embody the elements of the following sections.

### 9.6.1 SMC Roles and Responsibilities

A local SMC will be constituted for independent safety review of this trial. The SMC will review individual and cumulative participant safety data from each study sub-cohort when making recommendations regarding the safe continuation of the study. SMC members will not participate in the study, nor will they fall under the direct supervision of any investigator participating in the study.

PVS will, prior to any review of data, confirm that no conflicts of interest exist with any SMC member. Interests that might create a potential conflict of interest should be disclosed to

---

PVS prior to any review of safety data. PVS will determine if the relationship is in conflict or gives the appearance of a conflict such that the individual should not serve on the SMC. PVS will determine how to handle such potential conflict. PVS might dismiss a SMC member in the event of an unmanageable potential conflict.

The SMC membership will be considered confidential until after the study is completed.

### **9.6.2 Study Materials for SMC Review**

The primary focus of the SMC will be to independently review all SAEs and thoroughly investigate those considered unexpected. The SMC will accomplish this by evaluating all such events against the known or expected safety profile of the study vaccine. Clinical and laboratory data, clinical records, and other study-related records will be made available for SMC, as appropriate. If necessary, special reports will be prepared by the investigator or PVS.

It is the responsibility of the investigator and PVS to ensure that the SMC is apprised of all new safety information relevant to the study vaccines and the study. The SMC will receive all protocol revisions and might receive other documents related to the study.

### **9.6.3 Reports from the SMC**

The following reports might be submitted by SMC: review report and immediate action report.

#### **9.6.3.1 Review Report**

According to pre-specified criteria agreed upon by PVS, the SMC will communicate in writing its findings and any concerns and recommendations to the Sponsor and PVS. Unless otherwise specified, the written report will then be forwarded to the investigator who must, in turn, submit the report as per local IRB and IEC policy.

#### **9.6.3.2 Immediate Action Report**

The SMC will notify the Sponsor and PVS of any findings of a serious and immediate nature including any recommendations to discontinue all or part of the trial. PVS will immediately inform the investigator. In addition to any verbal communications, recommendations to discontinue or substantially modify the design or conduct of a study must be conveyed in writing on the day of the SMC meeting where this recommendation is formally made. This written, confidential report might contain unmasked supporting data and should include the SMC's rationale for the recommendations.

---

## 10 Clinical Monitoring

### 10.1 Site Monitoring Plan

Qualified and appropriately trained individuals from PVS or designated by PVS will carefully monitor the study. The study monitors will periodically contact the site and perform on-site visits. The extent, nature and frequency of site visits will be based on such considerations as study objectives, study design and complexity, and enrollment rate; periodicity and nature of monitoring activities will be described in the *Monitoring Plan*. PVS might also include representatives of IEM and/or Microgen in site contacts and visits, as appropriate, but will nevertheless keep officials from IEM and Microgen apprised of study progress.

